#### Blinding and unblinding

The study will be blinded for treatment so that the patient and the assessor of the neurological assessment and gait analyses are unaware of the treatment group assigned. The randomization list will be opened after the study database has been locked.

### Statistics

#### Study sample size

Sample size calculation is usually based on an effect size expected from a given treatment. Due to a lack of knowledge about the effects of EWST on sensory (SF) and motor functions (MF), such an estimation is limited. For this reason, a so-called adaptive design was chosen, corresponding to the “multi-arm multi-level approach” (MAMS approach) proposed by Jaki et al. [65]. The advantage of this design is that the effect size needed to calculate the sample size is not based on specific values, but on probabilities (*p* and p0) that can be used to identify the desired or the uninteresting effect. The probability *p* = 0.6 chosen for the study for the desired effect means that a randomly selected person in the treatment group has a 60% probability of achieving a better result than a randomly selected person in the control group. The uninteresting effect is assumed with a probability of p0 = 0.5. This value means that both the novel treatment and the placebo treatment perform equally well (Jaki et al., 2019). Another advantage of MAMS is that this form of sampling does not require any knowledge of the variance of the endpoint variables. All the calculations required for this are implemented in an R package and published accordingly (Jaki et al., 2019).

A two-armed, three-stage adaptive study design is envisaged at Neurowave. In stage 1 and stage 2, interim evaluations are carried out to determine whether the study can already be terminated. This will be the case if either the intended and thus desired result can already be sufficiently confirmed, or it becomes apparent that the study will not be a success. These interim evaluations offer the opportunity to shorten the study. If none of these two cases occur, the study will continue up to stage 3. The overarching advantage of this design is that the smallest possible number of patients can be found to demonstrate a medically relevant effect.

With a one-sided error rate of 5% and a planned power of 80%, the following design parameters could be calculated. For the upper and lower limits, the triangle test is selected [65].

**Table Taba:** 

	Stage 1	Stage 2	Stage 3
Cumulative sample size (control):	41	82	123
Cumulative sample size (treatment):	41	82	123
Maximum total sample size: **246**			
Upper bound	2.13	1.89	1.85
Lower bound	0.00	1.13	1.85
*p*-value for H1 ((stopping for) success)	0.018	0.031	0.033
*p*-value for H0 (stopping for a lack of efficacy)	0.500	0.130	
Continue as planned at stage 1: 0.500 > *p* > 0.018			
Continue as planned at stage 2: 0.130 > *p* > 0.031			

The calculation was done with the R package MAMS

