## Methods

This is a two-arm three-stage adaptive, prospective, multi-center, randomized, blinded, placebo-controlled clinical trial according to the MPG (Medizinproduktegesetz [Medical Devices Act]) which is designed as a two-arm three-stage adaptive trial.

Fourteen treating hospitals and three rehabilitation centers in Austria and Germany will participate. The allocation of the study groups will occur by means of a block randomization, in order to guarantee the best possible balance between the treatment group, the control group, and the treating hospitals. The study groups are comprised of a treatment group (extracorporeal shock wave therapy by means of electrohydraulic shock wave generation) and a control group (placebo ESWT).

To gain as homogenous groups as possible, a stratified block randomization with a block size of four will be done. The assignment to treatment and placebo group will be made in a ratio of 1:1. For stratification, three different neurological levels of injury will be used:
Cervical injuries: C1–C8Thoracic and lumbar injuries (T1–L1)Peripheral nervous system injuries (cauda equina and conus medullaris syndromes [35]; L2–S5)

Recruitment of patients takes place continually at admission to acute care in one of the 14 participating hospitals (13 in Austria, 1 in Germany). Patients and assessors of study relevant data are blinded to group allocation. The operating room staff and persons involved in the application of the study intervention are not blinded to group allocation and are required to keep it as a secret.

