**H1: delta.TMSC treatment group > delta.TMSC control group**

**H0: delta.TMSC treatment group < = delta.TMSC control group**

Assuming that the data are normally distributed and that an ANOVA is robust against violations of the normal distribution, a randomized complete block design ANOVA is performed to compare the mean delta differences between the two groups. The three different neurological levels for stratification will be the block variable. Furthermore, the mean values of all subscores with their 95% confidence intervals are displayed per group. In addition, charts are created based on descriptive analysis to capture results at a glance.

Note: A problem with spinal trauma is that it usually occurs because of external force (e.g., car or motorcycle accident, fall from a great height) and is simultaneously associated with injuries to the extremities. Consequently, due to the chosen treatment strategy for the affected extremities (e.g., plaster, orthosis, surgical dressing), baseline measurements cannot be performed on them. To avoid bias in the study results as much as possible, these affected subscores will not be included in the calculation of the composite endpoint, even if the score is recorded at follow-up.

Sensitivity analysis (SA) is also performed to assess the robustness of the analyses. In particular, the effects of outliers and missing data will be the focus of this SA.

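### The stop/go rule needs a one-sided p-value, but the only named test is an ANOVA whose ordinary p has no direction; separately, the printed cut-offs give about 5.2% type I error instead of 5%

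*Protocol article*

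**What the plan says.** All places are in the protocol article; no separate analysis plan is shown.

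- **Study sample size** sets the targets: "With a one-sided error rate of 5% and a planned power of 80%, the following design parameters could be calculated". The boundary shape follows: "For the upper and lower limits, the triangle test is selected". The effect of interest is p = 0.6, defined by comparing one patient drawn from each arm: "a randomly selected person in the treatment group has a 60% probability of achieving a better result than a randomly selected person in the control". For the null value, the section adds: "The uninteresting effect is assumed with a probability of p0 = 0.5".
- **The design table** below it lists 41, 82 and 123 patients per arm, upper bounds 2.13/1.89/1.85 and lower bounds 0.00/1.13/1.85. It adds p cut-offs of 0.018/0.031/0.033 for success and 0.500/0.130 for lack of efficacy. The decision rule is then put on p: "Continue as planned at stage 1: 0.500 > *p* > 0.018", with a matching line for stage 2 (0.130 and 0.031).
- **Hypothesis formulation and testing procedure** states a directional alternative (change in the total score larger under treatment than under control). It then names the test: "a randomized complete block design ANOVA is performed to compare the mean delta differences between the two groups", with the three neurological levels as blocks.
- **Methods** fixes the allocation: "The assignment to treatment and placebo group will be made in a ratio of 1:1".

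**The concern.** A futility cut-off of 0.500 at a bound of 0.00 makes sense only for a one-sided p-value. The group p-value that an ANOVA ordinarily reports is a function of the squared statistic: it is small for a large difference in either direction and near 1 when the arms are equal. The article does not say that this p is made one-sided or that the sign is checked.

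This p decides whether the trial stops at 82, 164 or 246 patients. If the unsigned p went into the printed rule, the rule would disagree with the bounds beside it in both directions. A clearly worse result under treatment could cross the success limit, and a modest benefit could be stopped for lack of efficacy.

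The second question is whether the printed p cut-offs hold the stated 5% error.

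**Working it through.** **Inputs.** One-sided alpha 0.05, power 80%, three stages, triangular bounds, P(better) = 0.6, 41 per arm per stage, 1:1 allocation. All are from Study sample size, the design table and Methods.

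**1. Reproduce the design.** With normal data, P(better) = 0.6 corresponds to a standardized difference of √2 × z(0.6) = 1.4142 × 0.2533 = 0.358. Triangular bounds are u_j = C(1 + j/3)/√j and l_j = C(j − 1)/√j. Solving for overall one-sided alpha 0.05 by recursive integration gives C = 1.599.

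- Upper: 1.599 × 1.333 = 2.132; 1.599 × 1.667/1.414 = 1.885; 1.599 × 2/1.732 = 1.847.
- Lower: 0; 1.599/1.414 = 1.131; 1.847.
- Power: 0.808 at 41 per arm per stage and 0.799 at 40.

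The design therefore reproduces. The printed 1.89 for 1.885 is a last-digit difference only.

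**2. Where the p cut-offs come from.** One-sided tail areas of the unrounded bounds:

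| Bound | Normal tail | t tail (80/162/244 df) | Printed |
|---|---|---|---|
| 2.132 (success, stage 1) | 0.0165 | 0.0180 | 0.018 |
| 1.885 (success, stage 2) | 0.0297 | 0.0306 | 0.031 |
| 1.847 (stage 3) | 0.0324 | 0.0330 | 0.033 |
| 0 (futility, stage 1) | 0.500 | 0.500 | 0.500 |
| 1.131 (futility, stage 2) | 0.129 | 0.130 | 0.130 |

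All five printed values are the t tails. The bounds, however, were calibrated as normal critical values. On the normal scale the printed success cut-offs correspond to z = 2.097/1.866/1.838, slightly looser than 2.132/1.885/1.847.

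**3. Operating characteristics with a one-sided p** (simulated with 1,000,000 trials, normal data, two-sample t).

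- Printed cut-offs: type I error 0.052 (0.0520 by recursion), power 0.809.
- Normal-tail cut-offs: type I error 0.050, power 0.806.

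The simulation standard error near 0.05 is √(0.05 × 0.95/1,000,000) = 0.0002, so the excess of 0.002 is not noise.

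**4. Worst case: the ordinary ANOVA p entered literally.** With two arms F = t², so this p is two-sided. On the normal scale the printed cut-offs become |Z| > 2.37/2.16/2.13 for success and |Z| < 0.67/1.51 for futility. Three stage 1 results show the conflict with the printed bounds:

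- Z = −2.5: p = 2 × 0.0062 = 0.012, below 0.018, so success. The bound says stop for lack of efficacy.
- Z = 0.5: p = 2 × 0.309 = 0.62, above 0.500, so stop. The bound says continue.
- Z = 2.2: p = 2 × 0.0139 = 0.028, so continue. The bound says success.

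Simulated results for this reading:

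- Under H0, total rejection is 0.050, split 0.025 for treatment and 0.025 against it.
- At the design effect, power is 0.67.
- With an equal effect in favour of control, the success limit is met with probability 0.67.
- Stage 1 futility at the design effect is 16%. By hand, mean Z = 0.358 × √(41/2) = 1.62 and P(|Z| < 0.674) = Φ(−0.95) − Φ(−2.30) ≈ 0.16. By design it is P(Z < 0) = Φ(−1.62) ≈ 0.05.

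**The case against.** The case against has real weight, and most of it stands.

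- **Direction is settled in intent.** The error rate is declared one-sided, H1 and H0 are directional, the 0.500 cut-off fits only a one-sided p, and signed bounds stand beside each p. The article nowhere says F-test or two-sided. With two arms, the ANOVA group effect converts exactly to a signed one-sided t-test. A reader might infer that the trial as planned has only 67% power or would declare harm a success. The article does not support that: those figures describe a literal misreading. What survives is that the named test and the rule do not fit together as written, and no sentence joins them.
- **The cut-offs are not misprints.** A reader might infer that the p-values contradict the bounds, or that the two can give opposite decisions. For a t statistic they do not. A one-sided p of 0.0175 on 80 df is t = 2.145, which exceeds 2.13, so bound and p agree. What survives is the small excess in error from using normal-theory bounds as t quantiles.
- **Converting software output to a one-sided p belongs in an analysis plan.** This would answer a complaint about omitted detail. Here, though, the article itself fixes both the p rule and the test, and the mismatch lies between those two statements.

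**Conclusion.** The point holds in two parts of unequal weight.

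The main part is a mismatch of wording at the decision rule: one-sided cut-offs are attached to a test whose ordinary p-value has no direction. The intended reading is recoverable and delivers power of about 0.81. The consequences of the literal reading (power 0.67, stage 1 futility 16% instead of 5%, success declared for an equal harm with probability 0.67) are a worst case, not a forecast. They are large enough that the rule should not be left to inference.

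The minor part is that the printed cut-offs, used with a one-sided t-based p, give an overall type I error of about 5.2% against the stated 5%. This does not threaten the design, and the planned 80% power is met.

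The figures assume normal data with equal variances. Blocking was not modelled; losing two further degrees of freedom changes the t tails by less than 0.0001.

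**What to change.** 1. Add one sentence to the design table and to the testing procedure: p is the one-sided p-value of the signed treatment-minus-control contrast from the block ANOVA, in the direction of H1. Stating the rule on the signed statistic against the bounds would also settle direction.
2. Replace the cut-offs by the normal tails of the bounds: success 0.0165/0.0297/0.0324, futility 0.500/0.129.
3. Change the two continuation lines to match: stage 1, p between 0.0165 and 0.500; stage 2, p between 0.0297 and 0.129.

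The cost is one sentence, four table entries and two lines. Type I error becomes 0.050 and power about 0.806 (from 0.809), and the sample size stays at 246. The change should be in place before the first interim analysis is read.

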#### Randomization

The randomization will be done with https://www.randomizer.at/, a tool that is provided by the MED UNI Graz.

#### Data analysis

##### Calculation of the composite endpoint

In general, following the intention-to-treat (ITT) approach, all patients are included in the analysis. For scale variables, the means, standard deviations (SD), median values, and minimum/maximum values will be given. For ordinal variables, medians and minimum/maximum values will be calculated and reported. Frequencies and percentages will be given for nominal variables. Missing values are not considered when calculating the percentage.

The International Standards for the Neurological Classification of Spinal Cord Injuries (ISNCSCI) was chosen as the relevant clinical endpoint for this study. This score includes several subscores, which are listed in the table below.

**Table Tabb:** 

**Motor scores (MS)**	
“Upper Extremity Motor Score” (**UEMS**) UEMS = UEL + UER	“Lower Extremity Motor Score” (**LEMS**) LEMS = LEL + LER
“Upper Extremity Left” (UEL)	“Lower Extremity Left” (LEL)
“Upper Extremity Right” (UER)	“Lower Extremity Right” (LER)

**Table Tabc:** 

**Sensory scores (SS)**	
“Light Touch Total”(**LTT**)	“Pin Prick Total”(**PPT**)
LTT = LTL + LTR	PPT = PPL + PPR
“Light Touch Left” (LTL)	“Pin Prick Left” (PPL)
“Light Touch Right” (LTR)	“Pin Prick Right” (PPR)
**ISNCSCI score = UEMS + LEMS + LTT + PPT = TMSC** (**T**otal **M**otor and **S**ensory S**c**ore)	

If the study were to use each of these ISNSCI subscores separately as endpoints for hypothesis testing, alpha error correction would need to be applied because of multiple testing. However, this necessity implies a loss of power with the consequence that a larger sample would be needed to demonstrate the desired effect.

Due to the expected low incidence of spinal injuries that may ultimately be included in the study, it is already difficult to achieve the required sample size. For this reason, the ISNCSCI subscores are combined into a composite endpoint to avoid the necessity of an alpha error correction. With this approach, we follow the recommendations of the “U.S. Department of Health and Human Services Food and Drug Administration” (source: https://www.fda.gov/regulatory-information/search-fda-guidance-documents/multiple-endpoints-clinical-trials-guidance-industry).

However, to understand the treatment effect as best as possible independent of the hypothesis test, all subscores are exploratively analyzed and discussed.

For the final endpoint, however, the ISNCSCI score was not used, but an INSCSCI difference score that was determined from the baseline and follow-up measurements after 6 months. To avoid confusion, we will call this score “delta.TMSC.” The use of such a difference score simplifies the testing of the hypothesis and enables an uncomplicated description of the direction and type of the occurring change in the data [66, 67].

**Composite Endpoint: delta.TMSC = TMSC after 6 month - TMSC at baseline**

The entire measuring process is illustrated in the following figure.

[figure not shown]

##### Hypothesis formulation and testing procedure

The aim of longitudinal assessments is to look for improvements over time. The treatment group is expected to achieve better results than the control group. To demonstrate the indicated treatment success, the delta.TMSCs is used.

Based on this score, the following hypotheses will be tested:

**H1: delta.TMSC treatment group > delta.TMSC control group**

**H0: delta.TMSC treatment group < = delta.TMSC control group**

Assuming that the data are normally distributed and that an ANOVA is robust against violations of the normal distribution, a randomized complete block design ANOVA is performed to compare the mean delta differences between the two groups. The three different neurological levels for stratification will be the block variable. Furthermore, the mean values of all subscores with their 95% confidence intervals are displayed per group. In addition, charts are created based on descriptive analysis to capture results at a glance.

Note: A problem with spinal trauma is that it usually occurs because of external force (e.g., car or motorcycle accident, fall from a great height) and is simultaneously associated with injuries to the extremities. Consequently, due to the chosen treatment strategy for the affected extremities (e.g., plaster, orthosis, surgical dressing), baseline measurements cannot be performed on them. To avoid bias in the study results as much as possible, these affected subscores will not be included in the calculation of the composite endpoint, even if the score is recorded at follow-up.

Sensitivity analysis (SA) is also performed to assess the robustness of the analyses. In particular, the effects of outliers and missing data will be the focus of this SA.

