### Study population

Included are female and male patients with an acute spinal cord lesion regardless of the neurological level of the lesion. Patients with either complete (AIS A) or incomplete (AIS B–D) lesion are included. A minimum age of 18 years must be reached at enrollment. No other age limit was defined. A gender distribution in favor of male patients is expected due to the higher incidence (men/women = 3.8/1) of traumatic SCI [4].

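### The primary ANOVA of delta.TMSC fixes the baseline slope at 1 and omits AIS grade; an ANCOVA would gain precision at almost no cost, although the planned test is valid

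*Protocol article*

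**What the plan says.** All references are to the protocol article.

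- **Primary test** (Hypothesis formulation and testing procedure): "a randomized complete block design ANOVA is performed to compare the mean delta differences between the two groups". The three neurological levels are the block, and no other term is named. The sensitivity analyses announced there concern outliers and missing data.
- **Reason for the change score** (Calculation of the composite endpoint): "The use of such a difference score simplifies the testing of the hypothesis". The same section says that the required sample size is already hard to reach.
- **Population** (Study population): "Patients with either complete (AIS A) or incomplete (AIS B–D) lesion are included".
- **Randomisation** (Methods): "For stratification, three different neurological levels of injury will be used". AIS grade is not a stratification factor.
- **Baseline data** (Study procedures): the AIS/ISNCSCI examination belongs to the baseline visit, before the intervention.
- **Other covariates**: CCI and ISS are described as possible or actual explanatory variables, and AIS classification is listed under secondary endpoints and control variables. None of them is placed in the primary model.

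**The concern.** Subtracting baseline is a form of adjustment, but one with the slope set to 1. On a bounded sum score the slope of 6-month TMSC on baseline need not be 1; wherever it is not, delta.TMSC still depends on baseline and that variation stays in the error term. AIS grade is neither balanced by design nor modelled, so its contribution to the variance, beyond what neurological level captures, also stays in the error term.

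At stake is precision in a trial that says patients are scarce and that chose a composite endpoint to save power. A second consequence is that a chance difference in severity between the arms moves the estimate uncorrected, including at the interim with 41 per arm, where the trial can stop in either direction. The model is fixed in the text, so this is not a detail left to an analysis plan.

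**Working it through.** **Inputs from Study sample size and its table.** "With a one-sided error rate of 5% and a planned power of 80%, the following design parameters could be calculated". "The probability *p* = 0.6 chosen for the study for the desired effect"; "The uninteresting effect is assumed with a probability of p0 = 0.5". Triangular bounds: upper 2.13/1.89/1.85, lower 0.00/1.13/1.85. Cumulative sample size 41/82/123 per arm, maximum 246. No SD is given: "this form of sampling does not require any knowledge of the variance of the endpoint variables".

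**Step 1: reproduce the design.** Under normality the standardised effect is √2·Φ⁻¹(0.6) = 1.414 × 0.2533 = 0.358. The upper bounds are c(1 + r/3)/√r and the lower bounds −c(1 − r)/√r for r = 1, 2, 3. Solving for one-sided alpha 0.05 gives c = 1.599, with upper bounds 2.13/1.88/1.85 and lower bounds 0.00/1.13/1.85. Power is 79.9% at 40 per arm per stage and 80.8% at 41. The plan's 41 and 246 are confirmed. With the bounds as printed, alpha is 0.0497.

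**Step 2: effect of adjustment.** The 0.358 is read in units of the within-level SD of delta.TMSC. If baseline TMSC and AIS explain a share R² of that variance, the effect becomes 0.358/√(1 − R²). The R² values are assumptions. With the same bounds and 41 per arm per stage:

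| R² | Effect | Power | Expected N at design effect | False futility stop at stage 1 |
|---|---|---|---|---|
| 0% | 0.358 | 80.8% | 150.1 | 5.2% |
| 2% | 0.362 | 81.5% | 149.5 | 5.1% |
| 5% | 0.368 | 82.5% | 148.5 | 4.8% |
| 10% | 0.378 | 84.3% | 146.8 | 4.4% |
| 20% | 0.401 | 87.8% | 142.5 | 3.5% |
| 30% | 0.428 | 91.2% | 137.1 | 2.6% |

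**Step 3: baseline TMSC alone.** Let k be the ratio of the 6-month SD to the baseline SD and ρ the correlation (both assumed). The large-sample variance ratio of ANCOVA to change score is k²(1 − ρ²)/(1 + k² − 2ρk), which never exceeds 1.

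- k = 1: the ratio is (1 + ρ)/2. For ρ = 0.5/0.7/0.9 it is 0.75/0.85/0.95, with power 89.5/86.0/82.5%.
- k = 1.2, ρ = 0.8: ratio 0.997, power 80.9%, so almost no gain.
- k = 0.8, ρ from 0.5 to 0.95: power 93 to 97%.

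**Step 4: chance imbalance in AIS at stage 1.** Assume half the patients are AIS A, and that AIS A and B–D differ by 1 within-level SD in mean change. The between-arm difference in AIS A share has SD √(2 × 0.25/41) = 0.110, which shifts the estimate by 0.110 SD. That variance is 0.110² = 0.0122. The full stage-1 variance is 2/41 = 0.0488. The ratio is 0.25, exactly the R² implied by a 50:50 split and a 1 SD gap (0.5 × 0.5 × 1²). The imbalance is therefore the Step 2 variance seen from another side.

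Conditional on the imbalance it still matters. The remaining SD of the estimate is √(0.0488 × 0.75) = 0.191. At the design effect the chance of falling below the stage-1 lower bound of 0 is Φ(−0.358/0.191), about 3%, with balanced arms. It is Φ(−0.248/0.191), about 10%, with a 1-SD adverse imbalance. The unconditional figure is the 5.2% in the table. Adjustment would hold it near 3% whatever the imbalance.

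**The case against.** The strongest reply is that nothing here is an error. A blocked comparison of change scores in a 1:1 randomised trial controls type I error, is unbiased over randomisations and reaches its stated power. That stands in full.

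Three stronger readings are tempting, and the documents support none of them:

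- *The analysis ignores baseline TMSC.* It does not; it subtracts it. What is missing is an estimated slope.
- *AIS imbalance adds bias on top of the power loss.* Under the Step 4 assumptions the 0.110 SD shift, or 0.216 SD at its 95% limit, is 31% to 60% of the planned 0.358. Step 4 shows that this is sampling variance already counted in the 80.8%.
- *AIS is the main prognostic factor, and half of this trial will be AIS A.* The protocol does not say the first. The figure of more than half in its Background is general epidemiology; the trial admits only awake, oriented patients and excludes complete cord transection.

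Two further points stand in part. If patients gain little at both ends of the scale, a linear baseline term may explain little; AIS grade as a categorical term meets some of this, but the documents give no recovery pattern. Subscores that cannot be examined at baseline are dropped, so baseline TMSC has a different maximum in different patients and the covariate must be built with care.

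Supportive adjusted analyses may exist in an unseen analysis plan. That would not change the primary model fixed here.

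**Conclusion.** The point holds as a specific improvement to a valid plan. The primary model leaves out two variables measured before treatment, one of which is not balanced by the randomisation either. The sample size of 246 is correctly derived and needs no change.

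The gain in power at that maximum runs from under 1 point (R² of 2%) to about 10 points (R² of 30%). Every such figure rests on an assumed R², or on an assumed correlation and SD ratio, so only the direction is firm: in large samples the adjusted analysis is at least as precise. False futility stopping at the first interim improves modestly on average, from 5.2% to between 5.1% and 2.6% over the same range. Confidence is high for what the model contains and low for the size of the loss.

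**What to change.** Before the first interim analysis, define the primary model as an ANCOVA of delta.TMSC on treatment, neurological-level stratum, baseline TMSC and baseline AIS grade (categorical). Using 6-month TMSC as the outcome is equivalent, provided that it is restricted to the same subscores. State that baseline TMSC is the sum of exactly those subscores that enter the patient's delta.TMSC.

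Apply the existing triangular bounds to the treatment statistic of this model at both interims and at the final analysis. Keep the block ANOVA without covariates as a supportive analysis.

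The cost is a short text change and a few degrees of freedom. With 82 patients at stage 1, the block ANOVA leaves 82 − 4 = 78 error degrees of freedom. One baseline term and three AIS contrasts leave 74. No extra patients or data are needed.

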### Handling of missing, unused, or faulty data; drop-outs; and terminations

In order to counteract missing values as best as possible, the study will be carried out according to the GCP principle (Good Clinical Practice). Additionally, a regular evaluation of the collected data will take place. If missing values are detected, an attempt will be made to subsequently determine them and/or to document the reasons.

Missing values concerning the primary endpoint are estimated according to the Last Observation Carry Forward principle (LOCF). If possible, the same procedure is used for the secondary endpoints. In all other cases, an analysis of the observed data will be carried out.

The systematically documented reasons for drop-outs will be evaluated to see if they can be used as a predictor for the endpoints and thereby additional insights into the therapy can be gained.

A sensitivity analysis will be performed in order to estimate the effect of missing data and outliers on the study endpoints.

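### Dropping subscores untestable at baseline scores their change as zero, so deltas of unequal range are averaged in one ANOVA and the treatment effect is diluted

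*Protocol article*

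**What the plan says.** The tables under Calculation of the composite endpoint define the total as a plain sum: "ISNCSCI score = UEMS + LEMS + LTT + PPT = TMSC". The endpoint is its change: "delta.TMSC = TMSC after 6 month - TMSC at baseline". Under Hypothesis formulation and testing procedure, "a randomized complete block design ANOVA is performed to compare the mean delta differences between the two groups", with the three neurological levels as the block variable.

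The Note in that section observes that spinal trauma often comes with limb injuries. When a limb is in plaster, an orthosis or a dressing, "baseline measurements cannot be performed on them", and so "these affected subscores will not be included in the calculation of the composite endpoint, even if the score is recorded at follow-up". The stated purpose is to limit bias.

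The section on missing data says that "Missing values concerning the primary endpoint are estimated according to the Last Observation Carry Forward principle (LOCF"), and both sections promise a sensitivity analysis on missing data and outliers. The exclusion criteria remove patients whose serious concomitant injuries prevent the initial neurological assessment.

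**The concern.** In an unweighted sum, leaving a component out of both time points is the same as entering a change of 0 for it. No rescaling, imputation, baseline covariate or minimum testable range accompanies the rule. A patient with an untestable limb therefore contributes a change on a shorter scale, and that change is averaged with full-scale changes. The resulting mean difference is not the difference in total motor and sensory change that the Primary endpoint section defines. The same quantity drives both interim decisions and the final test, in a trial planned at 80% power whose authors already expect difficulty in reaching the sample size.

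The unit of deletion is also open. Motor subscores exist per limb (UEL, UER, LEL, LER), but sensory subscores exist only per body side (LTL, LTR, PPL, PPR) or in total. There is no limb-level sensory subscore. Read literally, one leg in plaster could remove the light-touch and pin-prick scores for that whole side of the body.

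**Working it through.** **1. Reproduce the plan's design.** Inputs from Study sample size: "With a one-sided error rate of 5% and a planned power of 80" per cent, triangular bounds, three stages, and an effect under which "a randomly selected person in the treatment group has a 60% probability of achieving a better result". For normal data this effect is a standardised difference of √2 × z(0.6) = 1.414 × 0.2533 = 0.358. The triangular bounds are u_j = c(1 + j/3)/√j and l_j = −c(1 − j)/√j. Solving c for one-sided alpha 0.05 gives upper bounds 2.13/1.88/1.85 and lower bounds 0.00/1.13/1.85. The size needed is 40.1 per arm per stage, rounded up to 41, so 41/82/123 per arm and a maximum of 246. This matches the plan's table except for 1.88 against a printed 1.89. With the printed bounds, alpha is 0.0497 and power 0.807.

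**2. Share of the scale lost (w) for one injured leg.** The document gives no maximum scores. Assumed: 25 motor points per limb and 56 points per side for each of light touch and pin prick, so the total is 4×25 + 4×56 = 324.
- Motor subscore of that leg only: 25/324 = 8%.
- Plus light touch and pin prick of that side: (25 + 56 + 56)/324 = 137/324 = 42%.
- Extreme reading, LEMS, LTT and PPT all dropped: (50 + 112 + 112)/324 = 274/324 = 85%.

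**3. Dilution of the raw effect.** Let a share f of patients be affected, and let their change scale by (1 − w), which assumes that recovery and effect are spread in proportion over the components. The raw mean difference is multiplied by (1 − f·w). At an assumed f = 20%, the loss is 0.2 × 0.077 = 1.5%, 0.2 × 0.423 = 8.5% or 0.2 × 0.846 = 17%.

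**4. Power.** The SD changes as well, because affected patients' changes shrink. With a full-scale SD of 1 and an arm mean μ, the arm variance is [(1 − f) + f(1 − w)²](1 + μ²) − [(1 − f·w)μ]². Example with f = 20%, w = 42.3% and control mean 1.5:
- Control variance: 0.8666 × 3.25 − 1.373² = 0.931.
- Treated variance (μ = 1.858): 0.8666 × 4.453 − 1.701² = 0.966.
- Pooled SD: 0.974.
- Standardised effect: 0.358 × 0.915/0.974 = 0.337.
- Power with the printed bounds at 41 per arm per stage: 0.76.

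Power over mean control recovery of 0 to 1.5 SD (assumed), against 0.81 with no deletion:

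| Affected (assumed) | 8% lost | 42% lost | 85% lost |
|---|---|---|---|
| 10% | 0.81 | 0.78–0.80 | 0.71–0.78 |
| 20% | 0.81 | 0.76–0.80 | 0.62–0.75 |
| 30% | 0.81 | 0.75–0.79 | 0.54–0.72 |

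**5. Does other text repair it?** LOCF needs an earlier observation, and none precedes baseline. The sensitivity analysis is generic and changes neither the primary test nor the interim decisions. The exclusion criterion lowers the number affected, but the Note still expects such patients in the analysis.

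**The case against.** The best defence is that the endpoint is a change score. Without a baseline, the change in that subscore was never observed, and adding a 6-month value alone would count preserved function as recovery. The rule avoids that error, and this part stands. The defect is the absence of any common scale, imputation or adjustment, not the refusal to use an unpaired follow-up value.

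The rule also depends only on status before treatment, in a randomised trial with blinded assessors. A reader might infer that it biases the comparison towards one arm or inflates type I error, but nothing in the document supports that. The expected harm is a diluted effect, plus noise if limb injuries are unevenly distributed by chance.

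The size is uncertain too. The protocol says neither how many patients are affected nor at which level deletion occurs, and if only one limb's motor score goes, the loss of power is negligible. Subscores are also reported separately with confidence intervals, which helps interpretation but leaves the primary test as it is.

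Finally, one may say that such detail belongs in an analysis plan that is not shown. That would answer an omission. Here the protocol states a specific rule, and the concern is with that rule.

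**Conclusion.** The concern holds as a should-fix. The unequal ranges and the zero-change scoring follow from the protocol's own definitions and need no assumption. The dilution of about f × w also assumes that effect is spread in proportion over the components. The loss of power rests further on the assumed score maxima, affected share and control recovery. At 20% affected it runs from none (one limb's motor score), through 0.76–0.80 (that side's sensory scores also lost), to 0.62–0.75 under an extreme reading that no section prescribes.

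A reader might multiply the standardised effect by (1 − f·w) with the SD held fixed and conclude that power falls to 74% in the 42% case. That is too pessimistic, because the SD shrinks as well, and 74% lies below the whole range for that case. Nor do the documents support reading a whole-side or whole-subscore loss as the stated rule, since they leave the level open.

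**What to change.** - In the Note, confine exclusion to the untestable myotomes and dermatomes instead of whole subscores, and state that level explicitly.
- Make the primary analysis the 6-month TMSC with baseline TMSC as covariate, keeping the neurological-level block. All 6-month items then count on one common scale.
- Multiply impute only the untestable baseline items, from pre-treatment information: testable baseline segments, neurological level and baseline AIS grade. Do not use the 24–72 h examination. It follows surgery, and the intervention is ideally given at skin closure, so imputing from it could absorb an early treatment effect.
- Keep the present deletion rule as a named sensitivity analysis.
- Reconcile the Note with the exclusion of injuries that prevent the initial assessment, so that it is clear which patients with limb injuries are expected in the trial.

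The cost is analysis wording and an imputation step, provided that ISNCSCI items are recorded individually. The downside is reliance on an imputation model for some baseline items. The change should be made before the first interim analysis at 41 patients per group.
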